**Fig. 4 Fig4:**
[figure not shown]
2 × 2 contingency table illustrating McNemar’s test for paired data to assess rates of change for the biomarker test, ArteraAI Prostate Test, on shared ADT decision making. Primary endpoint of proportion changing shared decision on use of ADT is calculated as (b + c) / (a + b + c + d)

Multivariate logistic regression analyses will also be used to assess the odds ratios (OR) of factors leading to the pre-test and the post-test ADT recommendations. Pre-test exploratory covariates can include age, ISUP grade, initial PSA, tumour stage and percentage of cores positive. Post-test covariates will also include the ArteraAI Prostate test results.

The study opened to enrolment in December 2023, and is expected to complete accrual in 2025.

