Several randomized controlled trials (RCTs) have investigated the use of short-term ADT (ST-ADT) in intermediate-risk prostate cancer, including RTOG-9408, EORTC 22,991, DFCI 95–096, and RTOG 0815 [3, 10–13]. While some of these trials have demonstrated improvements in biochemical control and, in some cases, reductions in distant metastases and cancer-specific mortality with the addition of ST-ADT, they often suffer from limitations such as the use of older radiotherapy techniques, heterogeneous patient populations, and an inability to precisely identify the subpopulation most likely to benefit from ADT. The D’Amico RCT highlighted comorbidity as a potential discriminator, suggesting that patients with moderate to severe comorbidities may not benefit from ST-ADT and may experience increased cardiac mortality [11, 12]. These findings underscore the need for better tools to guide personalized treatment decisions regarding ST-ADT in intermediate-risk prostate cancer.

The ArteraAI Prostate Test uses a multimodal AI (MMAI) architecture that encompasses both clinical and digital histopathology data. Multimodal deep learning uses combinations of various data modalities together, compared to a singular modal learning which would analyse each of these independently. The clinical features of this model consist of: age, PSA, Gleason combined, Gleason primary, Gleason secondary, and T-stage. The second pipeline consists of digital histopathology, which was trained using a self-supervised learning model. This analyzes multiple image features using a neural network. Both the clinical and histopathology vectors are analysed together using a separate neural network to create a MMAI score, Fig. 1.

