### Methods

After providing informed consent, clinical variables including combined Gleason score, Primary Gleason Score, Secondary Gleason Score, clinical T-stage, baseline PSA, and age at biopsy are recorded. Next, a single formalin fixed, paraffin embedded (FFPE) hematoxylin and eosin-stained slide containing one biopsy core with the tumor that has the highest Gleason grade used by the local pathologist in making their diagnosis for the patient will be digitised.

When scanning is completed, a certified pathologist approved by Artera^®^ will review the digitally converted image to assess suitability for the MMAI biomarker test. The test will be run using locked AI models (v1.2) for the duration of the study. The locked models makes sure all participants will be assessed using the same models [23]. After completion of the test, the ArteraAI Prostate Test report will be verified by the certified pathologist and then made available to clinical staff via a web portal.

Figure 3 shows an example of the test report. Figure 3a displays an example of an NCCN unfavourable IR prostate cancer who is estimated to have a low prognostic risk for distant metastasis and low predictive benefit for the addition of ADT with radiotherapy using the ArteraAI Prostate Test. Figure 3b displays the other side of the spectrum with the ArteraAI Prostate Test estimating a high prognostic risk for distant metastasis and high predictive benefit for the addition of ADT with radiotherapy. Before the test result is available, the pre-test shared ADT decision result is captured. After the ArteraAI Prostate Test results are discussed between the clinician and patient, the post-test shared ADT decision result will be recorded. At a median follow-up of 5 years for the cohort, a data linkage with PCOR will be established to allow for assessment of quality of life and efficacy data (Table 2).

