### Statistical considerations

Given the novel nature of ASTuTE, it is not possible to estimate the event rate for the primary endpoint proportion change in shared decision making regarding use of ADT. If an incorrect estimate is used, there is a risk of underpowering the study. Therefore, an interim analysis will be performed at 200 participants. This will allow for early assessment into the rates of management change and help determine the final number of participants needed to adequately power the final analysis of the study. At this time, 800 participants are planned for enrolment, with final numbers to be determined at the time of the interim analysis.

The McNemar’s test will be used to analyse the primary endpoint. There is a rare chance that the number of pre- to post-test recommendations of Yes-No and No-Yes is equal. This could lead to the null hypothesis being retained when the ArteraAI Prostate test is actually outperforming standard of care. As such, the study is designed to be hypothesis-generating, rather than focusing on a specific hypothesis that would define the sample size. This trial of implementation which assesses rates of management change based on a biomarker test has been used in recent literature. The DCISionRT^®^ study, used this approach to assess a breast genomic biomarker impact on radiation therapy recommendations [24].

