### Data analysis plan

Simple statistical analysis will be performed by calculating “rates of change” with appropriate confidence intervals for changes in pre- and post-testing treatment recommendations. Summary statistics will be used to present the treatment recommendation pre- and post- incorporation of test results and secondary analyses.

For instance, in order to assess the impact of ArteraAI Prostate Test results on recommendations for shared ST-ADT use, the percentage change in recommendations will be calculated, and McNemar’s test for paired data will be used to assess the change in shared ST-ADT recommendations pre-test versus post-test, Fig. 4.

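### The exploratory post-test logistic model does not name the recorded pre-test recommendation, so its odds ratio for the test describes the final decision and not what the test changed

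*Protocol article*

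**What the plan says.** The Data analysis plan of the protocol article sets up multivariate logistic regressions to "assess the odds ratios (OR) of factors leading to the pre-test and the post-test ADT recommendations". On covariates it says: "Pre-test exploratory covariates can include age, ISUP grade, initial PSA, tumour stage and percentage of cores positive". The post-test model is distinguished by one sentence: "Post-test covariates will also include the ArteraAI Prostate test results". Neither sentence names the pre-test recommendation.

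That variable is available. The Methods section states: "Before the test result is available, the pre-test shared ADT decision result is captured". Table 2 schedules the shared ADT decision at both enrolment and post-test.

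The Background describes what the test is built from besides the digitised slide: "The clinical features of this model consist of: age, PSA, Gleason combined, Gleason primary, Gleason secondary, and T-stage".

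The plan assigns the impact of the test elsewhere. The Data analysis plan uses the percentage of recommendations changed and McNemar's test "for paired data will be used to assess the change in shared ST-ADT recommendations pre-test versus post-test". The Fig. 4 legend defines the primary endpoint as the discordant cells over all four cells of the paired table. Statistical considerations calls the study hypothesis-generating.

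**The concern.** The percentage changed and McNemar's test show how many decisions moved and in which net direction. They do not relate the movement to the test result. The post-test regression is the only analysis described that links the result to decisions, so readers will tend to take its OR as the influence of the test.

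As named, the model does not support that reading. A man's post-test recommendation depends heavily on his pre-test one. The pre-test decision can also carry matters that the listed covariates miss, such as comorbidity (which the Background itself discusses), patient preference and centre practice. Leaving it out has two possible consequences:

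- **Dilution.** When most decisions persist, a real effect of the test on the decisions that move is averaged over the many that do not.
- **Credit for decisions already made.** If the test result and the pre-test decision share information beyond the listed covariates, the OR can exceed 1 although nobody acted on the test.

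**Working it through.** The documents attach no figure to this regression, so there is nothing of the plan's own to reproduce. The check is by simulation. From the documents come N = 800 (provisional: "At this time, 800 participants are planned for enrolment, with final numbers to be determined at the time of the interim analysis") and the structure of the two models. All other inputs are assumptions.

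**Simulation A (400–500 trials per scenario).** The pre-test decision follows a logistic model with coefficient 0.5 on each of three measured covariates, plus an unmeasured term (coefficient 0.5 or 1.0 in re-runs). The test result has logit −0.65 + 0.4 × (sum of covariates), giving about 36% positive. Decisions flip with probability 15% (pre-test Yes, test negative), 10% (pre-test No, test positive) and 5% otherwise.

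Hand check of the ORs that these inputs imply:

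- Pre-test Yes men: final Yes is 0.95 if positive and 0.85 if negative. OR = (0.95/0.05)/(0.85/0.15) = 19/5.67 = 3.35.
- Pre-test No men: final Yes is 0.10 if positive and 0.05 if negative. OR = (0.10/0.90)/(0.05/0.95) = 0.111/0.0526 = 2.11.
- Ignoring the pre-test decision, with half of men pre-test Yes in both test groups: positive 0.5 × 0.95 + 0.5 × 0.10 = 0.525; negative 0.5 × 0.85 + 0.5 × 0.05 = 0.45. OR = (0.525/0.475)/(0.45/0.55) = 1.105/0.818 = 1.35.

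The simulated values agree with this. With 8.7% of decisions changing, the test OR is about 1.4 as planned and about 2.8 with the pre-test decision added. Power is about 50–54% and 96%. The Monte Carlo standard error near 50% is √(0.25/400) = 2.5 percentage points. In these runs the test has no link to the unmeasured term, so the dilution does not depend on one. In a large-effect scenario with 24% change, power is 100% with either model.

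**Simulation B (400 trials per scenario).** Five measured covariates; test 35% positive; an unlisted factor known to the clinician enters the test score with coefficient ρ and the pre-test decision with log-OR β. In the first four rows the test moves no decision and 10% flip at random. In the last three, 40% of decisions follow the test and 5% flip at random.

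| Test used? | ρ, β | OR as named | Rejections | OR with pre-test | Rejections |
|---|---|---|---|---|---|
| No | 0, 0 or 1 | 0.99 | 5–6% | 0.96–1.01 | 4–5% |
| No | 0.3, 0.5 | 1.19 | 16% | 0.98 | 5% |
| No | 0.5, 1 | 1.63 | 79% | 1.01 | 6% |
| No | 1, 1 | 2.14 | 99% | 0.97 | 6% |
| Yes | 0, 0 or 1 | 6.0–6.2 | 100% | 25.2–25.6 | 100% |
| Yes | 0.5, 1 | 8.9 | 100% | 25.4 | 100% |
| Yes | 1, 1 | 11.6 | 100% | 25.5 | 100% |

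In the last three rows the influence of the test is the same throughout. The OR as named nearly doubles as the shared information grows, while the adjusted OR stays put.

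**The case against.** **The list is open and the article is condensed.** The clinical covariates are exploratory and worded permissively, and a full protocol or SAP may name the pre-test recommendation. This stands in part: a reader might infer that the plan excludes the variable, and it does not. Still, the article does state what distinguishes the post-test model from the pre-test one, and the baseline decision is not in that statement.

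**The regression is descriptive.** Its stated aim is the factors leading to each recommendation, and the impact of the test is assigned to paired analyses that use the pre-test decision. This stands. A model without the pre-test decision is legitimate for that aim, and ORs of 1.4 and 2.8 answer different questions. The first is not an erroneous version of the second.

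**Clinical factors are not falsely flagged.** In Simulation A a covariate with no direct role in the change is significant in about 99% of runs as planned and in 4–6% with the pre-test decision. A reader might take this as a false-positive rate. It is not one: the covariate drives the pre-test decision, most decisions persist, and so it does lead to the final recommendation.

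**The false-positive result is assumed in.** The inputs that the test shares with the clinical record (age, PSA, grade, stage) are largely among the planned covariates, and the documents show no direct route from comorbidity, preference or clinician habit into the score. This stands as a limit. Spurious credit needs an extra link, for example imaging known to the clinician, and the documents do not establish one.

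**The power loss depends on the scenario.** This also stands. The only comparable overall change rate in the article is 42%, from a breast biomarker study, and the loss has already disappeared at 24%.

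**Conclusion.** The point holds as a limited weakness of an exploratory analysis. Without the pre-test recommendation, the test's OR is an association with the final recommendation and cannot be read as the test's contribution to changing it.

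The dilution needs only that most decisions persist. It costs 42 to 46 percentage points of power in the 8.7% scenario (96 − 54 and 96 − 50) and none at 24% change. Spurious credit for an ignored test is conditional on an unlisted shared factor, and its size (16% to 99%) rests on coefficients that the documents do not give.

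A reader might go further and infer that the trial's main result is biased, or that the test will be credited with decisions it did not alter. The documents do not support either inference: the primary endpoint and McNemar's test are paired and unaffected, and the second outcome is a possibility only.

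**What to change.** Keep the planned post-test model and label it a description of factors associated with the final recommendation. Beside it, add a post-test model with the same covariates, the test results and the pre-test recommendation, and state that the test's influence is read from this model only.

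An alternative is to fit post-test ADT separately in pre-test Yes and pre-test No men. The two are not identical: the single model imposes a common test OR, and the separate models do not. Under the Simulation A inputs the two strata have ORs of 3.35 and 2.11.

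The cost is one extra model and a sentence or two of text; the variable is already collected. The downside is interpretive. The pre-test decision lies between the clinical factors and the final recommendation, so clinical-factor ORs in the added model are conditional on that decision and do not describe their total association. That is why the added model should accompany the planned one and not replace it.

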## Discussion

The question about the benefit of ST-ADT amongst IR prostate cancer patients undergoing radiotherapy is challenging due to the known toxicity profile of ADT, large range of potential disease outcomes for IR prostate cancer and unknown impact at an individual level of ST-ADT. IR prostate cancer is a large spectrum for staging in prostate cancers with varied outcomes amongst them [25]. MDACC and MSKCC retrospective data [26, 27] supports benefit for ST-ADT in only the unfavourable IR (UIR) men. However, some cases can be turned into UIR merely by changing the biopsy targeting method. At a population level, the most mature data from randomised control trials looking at the benefit for ST-ADT in IR men are summarised in Table 3. The limitation from these trials are the use of older radiotherapy techniques, heterogeneous patient populations, and the inability to identify and exact subpopulations that are the ones to benefit from the addition of ST-ADT.

**Table 3 Tab3:** Pivotal ST-ADT randomised control trials for IR prostate cancer men

Trial Name	Number of patients, *n*	Intervention	Endpoints	Comments
**RTOG-9408** [3]	1086 IR men	66.6 Gy / 37 fractions ± 4 months of LHRH agonist with Flutamide	18 years bcF 57% woST-ADT 43% wST-ADT DSM 16% woST-ADT 9% wST-ADT	15 years PCSM: FIR vs. UIR 14% vs. 28% woST-ADT 9% vs. 12% wST-ADT DM: FIR vs. UIR 5% vs. 24% woST-ADT 8% vs. 10% wST-ADT
**EORTC 22,991** [10]	481 IR men	74 Gy / 37 fractions (71.1%) *or* 78 Gy / 39 fractions (28.9%) ± 6 months of LHRH agonist with bicalutamide for 7 days	12.2 years OS 74% woST-ADT 80% wST-ADT DM 27% woST-ADT 21% wST-ADT	
**RTOG 0815** [13]	1,492 IR men	79.2 Gy / 44 fractions (89%) *or* 45 Gy / 25 fractions with brachytherapy boost (11%) ± 6 months of LHRH agonist with antiandrogen for 10 days	8 years OS 79% woST-ADT 84% wST-ADT DM 4.3% woST-ADT 1.0% wST-ADT	− 67% having a single IR factor − 27% grade group 3 disease - excluded patients with more than two IR factors and ≥ 50% positive cores.
**DFCI 95–096** [11, 12]	153 IR men	70 Gy / 35 fractions ± 6 months of LHRH agonist with Flutamide	7 years OS with no or mild comorbidity 86% woST-ADT 91% wST-ADT OS with moderate or severe comorbidity 28.5% wST-ADT 62.5% wST-ADT	- Use of Adult Comorbidity Evaluation 27 comorbidity scores (ACE-27).
**PCS III** [28]	400 IR men	76 Gy / 38 fractions ± 6 months of LHRH agonist with bicalutamide	10 years PCSM 6.5% woST-ADT 1.5% wST-ADT DM 10% woST-ADT 3.5%% wST-ADT	-78% UIR -contained another randomisation arm of 70 Gy / 35 fractions wST-ADT, 200 IR men.

*Abbreviations*: IR - intermediate risk, LHRH - Luteinizing hormone–releasing hormone, bcF - biochemical failure, woST - ADT–without short–term androgen deprivation therapy, wST - ADT–with short–term androgen deprivation therapy, DSM - disease specific mortality, PCSM - prostate cancer specific mortality, FIR - favourable intermediate risk, UIR - unfavourable intermediate risk, DM - distant metastasis, OS - overall survival

Around 70% of men recover their testosterone from 6 months of ADT at 1.5 years from initial injection [29]. This is a lengthy time for reduced QoL and toxicity effects with some patients taking longer, or never recovering [30–33]. D’Amico et al. helped highlight the potential deleterious effects of ST-ADT in patients with moderate or severe comorbidity [11]. Although some of the effects on bone health and lean muscle mass can be proactively managed through serial DEXA imaging and exercise medicine, ideally only men most likely to derive meaningful benefit from ST-ADT would be exposed to these toxicities in the first place.

To better inform the clinician / patient discussion on ST-ADT better tools are required at the patient level to help personalise the anticipated benefit from ST-ADT. Implementation trials are becoming more necessary as technology evolves. DCISionRT^®^ was one of the first of these trials with the analysis of real world results on decision changes using a genomic biomarker. This trial was unique as it strongly showed how a validated biomarker can change clinical management decisions regarding the recommendation for adjuvant radiotherapy following breast conserving surgery in ductal carcinoma in situ (DCIS). Of the 539 women included 42% had changes to the adjuvant radiotherapy recommendation after this genomic biomarker test (46% yes to no, and 35% no to yes) [24]. Another implementation trial, GARUDA, characterised patients into low or high risk of developing late moderate to severe genitourinary toxicities following stereotactic body radiation therapy (SBRT) to the prostate by using a genomic biomarker test (PROSTOX). Of the 208 men included in this trial, 85% were classified as low risk and 15% as high risk. The vast majority of low risk patients, 98.8% chose SBRT, however, in the high risk cohort only 55.2% chose SBRT with the remainder choosing a moderately hypofractionated radiotherapy course (*p* < 0.001) [34].

A strategic objective in the ASTuTE trial was for the development of a robust platform where new technologies can be rolled out safely while assessing the degree of impact in a well-regulated environment. This opens the doors for a rapid adoption of machine learning, particularly in the context of digital histopathology. The ArteraAI prostate test has had the predictive model for ST-ADT validated [15] and the prognostic model validated [23]. It has outperformed the traditional NCCN classification, and is recommended as a tool in risk stratification with level 1B evidence. The ASTuTE trial will prospectively determine the utility of the ArteraAI Prostate Test in IR prostate cancer patients by measuring the rate of change in shared ST-ADT decisions and secondly will give more robust prospective data on efficacy whilst employing modern radiotherapy techniques. This is the first large scale deep learning technology to be employed to help guide prostate radiotherapy management and the success of this trial will enable other similar initiatives to follow suit

## Data Availability

No datasets were generated or analysed during the current study.
